## Abstract

**Background:**

Children with sensitization against foods have to be orally food-challenged before eating these foods for the first time. However, the waiting time for an oral food challenge (OFC) in Germany is about 3–6 months. In contrast, there are hints that an early introduction of allergenic foods might be protective regarding the development of food allergy. The aim of this clinical trial is therefore to investigate, whether an introduction and regular consumption of small amounts of food allergens is safe and will result in an increase of tolerance in children with sensitization against food allergens with unknown clinical relevance.

**Methods:**

In this randomized, placebo-controlled, double-blind, single-center trial, 138 children (8 months to 4 years of age) sensitized to the target allergen(s) hen’s egg, cow’s milk, peanuts, and/or hazelnuts with unknown clinical relevance will be randomized in a 1:1 ratio to either an active or a placebo group, daily receiving a rusk-like biscuit powder with or without the target allergen(s) for 3–6 months until an OFC will be performed in routine diagnostics. The primary endpoint is an IgE-mediated food allergy to the primary target allergen, after the interventional period.

**Discussion:**

Children with sensitization against food allergens with unknown clinical relevance often have to avoid the corresponding foods for several months until an OFC is performed. Therefore, the “window of opportunity” for an early preventive introduction of allergenic foods might be missed. This trial will assess whether an introduction of small allergen amounts will favor tolerance development in these children.

**Trial registration:**

German Clinical Trials Register DRKS00032769. Registered on 02 October 2023.

## Introduction

### Background and rationale {6a}

Up to 8% of all infants and children in industrialized countries suffer from food allergy with cow’s milk, hen’s egg, peanuts, and tree nuts being the main elicitors [1]. Infants with eczema are at particularly high risk for developing food allergies [2]. About half of children with eczema become sensitized, and about one-third will develop food allergy [1, 3, 4]. Many children show allergic reactions upon eating allergenic foods for the first time. The current understanding is that sensitization occurs via the cutaneous route due to an impaired skin barrier in these infants [2]. In the past, prevention strategies for food allergy have been driven by avoidance of allergenic foods in high-risk infants. Despite these attempts, a rising prevalence of food allergy has been observed [1, 5]. On the other hand, it has been shown that an early oral introduction of peanuts and baked hen’s egg can prevent the development of food allergies [6, 7]. Therefore, the current international as well as German guidelines, updated in 2021 and 2022, no longer recommend avoidance of highly allergenic foods [8, 9]. In contrast, for the prevention of hen’s egg allergy, well-cooked egg (e.g., baked or hard-boiled) should be early introduced with the complementary food and given regularly [8, 9]. However, so far, only a protective effect against allergy to well-cooked but not all kinds of egg preparations was shown [6]. For the prevention of peanut allergy, the international guidelines recommend an early introduction of peanuts for infants in countries with a high prevalence of peanut allergy [8]. In Germany, the introduction and regular consumption of peanuts in an age-appropriate form (e.g., peanut butter) may be considered in infants with atopic dermatitis living in families with regular peanut consumption [9]. Beforehand, peanut allergy should be ruled out, especially in infants with moderate to severe atopic dermatitis [9]. Therefore, the infant needs to be tested for sensitization (determination of specific IgE and/or skin prick test), and in case of sensitization, an oral food challenge (OFC) is recommended in order to determine its clinical relevance [10]. This crucial step in the diagnostic workup usually takes several months due to limited capacity for OFCs, because it is a time- and cost-consuming procedure, which can only be performed in specialized centers. Currently, the waiting time for an OFC throughout Germany is about 3–6 months. This is of high concern as the “window of opportunity” for the introduction of food allergens like peanuts and hen’s egg might be missed.

Moreover, for the prevention of other common food allergies in early childhood such as cow’s milk or hazelnut allergy, the best way of allergen introduction into the infant’s diet is still under debate [8, 9].

Therefore, the aim of this trial is to assess if the introduction and regular consumption of small amounts of cow’s milk, hen’s egg, peanuts, and/or hazelnuts is safe and effective in increasing tolerance in children of 8 months to 4 years of age with sensitization against these food allergens, which they have not consumed so far (sensitization without known clinical relevance).

This is an abridged protocol based on protocol version 1.0 dated 29 September 2023. The full protocol adheres to the Standard Protocol Items: Recommendations for Interventional Trials (SPIRIT) recommendations for interventional trials [11].

### Objectives {7}

The primary trial objective is to investigate the impact of an early introduction and continuous intake of small amounts of the target allergenic foods (cow’s milk, hen’s egg, peanuts, and/or hazelnuts) on the development of food allergy in sensitized children with unknown clinical relevance. Secondary objectives are to investigate if the introduction and continuous intake of small amounts of the target allergenic foods is safe in children with food sensitization of unknown clinical relevance, or if it results in an increased occurrence of allergic reactions or gastrointestinal problems. Moreover, the impact of an introduction and continuous intake of small amounts of the target allergenic foods on the development of multiple food allergies, the severity of eczema, the prevalence of asthma, and the immunoglobulin pattern in children with sensitization without known clinical relevance will be assessed.

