### Eligibility criteria {10}

Infants and children aged 8 months to 4 years with a sensitization (specific IgE (sIgE) ≥ 0.1 kU/l and/or skin prick test (SPT) wheal size ≥ 3 mm) against cow’s milk, hen’s egg, peanuts, and/or hazelnuts (target allergenic foods) and an already scheduled oral food challenge at the Charité – Universitätsmedizin Berlin (3–6 months after enrollment) for routine diagnostics are eligible for the trial. Infants are excluded from the study if they have previously consumed the target allergenic food they are sensitized to in relevant amounts. Further exclusion criteria are wheat allergy (study product contains wheat), severe other health issues (e.g., heart disease), a twin sibling already taking part in the study, and participation in another interventional trial.

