	**Interventional allergens**			
	**Peanut**	**Hazelnut**	**Hen’s egg**	**Cow’s milk**
**Amount of protein [mg/3 g] to be taken once daily**	1.7	1.9	1.8	2.0

The sugar-free, rusk-like biscuit powder (3 g of powder/day using a measuring spoon) will be mixed with water, and optionally fruits, to a puree. The study product should be eaten daily throughout the study duration. The first feeding of the study product at visit 1 (V1) will be performed under medical supervision at the study center. The duration of the intervention is determined by the date of the routinely scheduled OFC at visit 2 (V2) and should be at least 3 months and up to 6 months after inclusion to the trial. In case of a postponed OFC (e.g., due to illness of the child), the duration of the intervention can be extended up to a maximum of 9 months.

In the placebo group, subjects consume daily the same sugar-free rusk-like biscuit powder, however, without cow’s milk, hen’s egg, peanuts, or hazelnuts following the same instructions as the active group. To ensure blinding, the first feeding of the placebo study product will also be performed under medical supervision at the study site.

In infants, first, weaning foods (e.g., vegetables) should have been successfully introduced for at least 1 week before feeding the study product. Mothers will be encouraged to continue breastfeeding while introducing weaning foods. Parents of both groups will be advised to avoid cow’s milk, hen’s egg, peanuts, hazelnuts, or their products in their child’s diet according to the individual sensitization profile.

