#### Relevant concomitant care permitted or prohibited during the trial {11d}

All participants may continue their usual medications, as well as those taken for any concomitant diseases including wheezing and eczema throughout the study. All subjects who will undergo an oral food challenge at V2 will be advised to discontinue oral antihistamines 3–5 days before this procedure.

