#### Secondary endpoints

The following secondary endpoints will be assessed after 3–6 months (plus max. 3 months) of intervention (V2):IgE-mediated food allergy determined by OFC (plus sIgE ≥ 0.1 or positive SPT) to the “primary target food allergen”IgE-mediated food allergy determined by an immediate-type allergic reaction due to accidental exposure (plus sIgE ≥ 0.1 or positive SPT) to the “primary target food allergen”IgE-mediated food allergy determined by OFC (plus sIgE ≥ 0.1 or positive SPT) or an immediate-type allergic reaction due to an accidental exposure (plus sIgE ≥ 0.1 or positive SPT) to either of the following (for children sensitized to the respective allergen at baseline):Hen’s eggCow’s milkPeanutsHazelnutsOccurrence (frequency and severity) of immediate type allergic symptomsOccurrence of gastrointestinal symptomsMultiple food allergiesNumber of food allergiesChange to baseline of SCORAD (in subjects with eczema)Change to baseline of EASIscore (in subjects with eczema)WheezingAllergen-specific IgE to hen’s egg, cow’s milk, peanuts, and/or hazelnutsWheal size measured by skin prick testing to hen’s egg, cow’s milk, peanuts, and/or hazelnuts

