## Statistical methods

### Statistical methods for primary and secondary outcomes {20a}

The primary analysis of the primary endpoint will be performed by logistic regression with (fixed) factor treatment group (verum, placebo regarding the primary allergen) and the stratification factors primary allergen (hen’s egg, cow’s milk, peanuts, hazelnuts), age group (≤ 2, > 2 years of age), grade of sensitization (low, medium, and high), and planned duration of intervention (< 5, ≥ 5 months). In case of stratification groups with very few cases, stratification groups may be combined (e.g., low vs. medium/high grade of sensitization) or the factor omitted from the analysis model; the decision will be finalized, blinded, and described in the statistical analysis plan (SAP). From this model, the odds ratio for verum vs. placebo treatment will be calculated with a 95% confidence interval and a *p*-value for the treatment group comparison. The analysis will be performed on the full analysis set (FAS) based on the intention-to-treat principle without imputation of missing values. The significance level will be set to 0.05 (two-sided). All other analyses will be considered explorative. Several explorative sensitivity analyses will be performed for the primary endpoint: a re-run of the primary analysis model with the per-protocol population (instead of the FAS). In case of relevant differences between the treatment groups with respect to baseline variables, the primary analysis will be repeated with further adjustment variables (FAS population). To account for the potentially varying lengths of follow-up, a Cox proportional hazards regression as well as Poisson regression will be used to analyze the primary endpoint. Explorative analysis of secondary endpoints will follow the same principle as the primary analysis of the primary endpoint, i.e., models with the (fixed) factor treatment group and the stratification factors. Binary endpoints will be analyzed by logistic regression; continuous endpoints will be analyzed by analysis of covariance (ANCOVA) with the respective baseline value (if available) as an additional covariate. Secondary endpoints will be analyzed with the FAS. Regarding safety endpoints, the nature, frequency, and severity of adverse events and safety variables, including serious adverse events, will be summarized descriptively by treatment group (based on the safety population of all participants who received at least one dose of study treatment and have at least one post-baseline safety assessment, analyzed according to the treatment received). Further details will be described in the SAP, which will be finalized prior to data analysis.

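### The secondary objective promises asthma prevalence, but only wheezing is measured, and the stated model rule gives wheezing no baseline term

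*Protocol article*

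**What the plan says.** - **Objective.** Objectives {7} list among the secondary aims the impact on "the prevalence of asthma, and the immunoglobulin pattern".
- **Endpoint.** The Secondary endpoints list names no asthma outcome. The relevant stretch runs "Change to baseline of EASIscore (in subjects with eczema)WheezingAllergen-specific IgE", so the respiratory item is one word, with no definition and no statement of whether it means new or any wheeze.
- **Timing and age.** The list is introduced by "The following secondary endpoints will be assessed after 3–6 months (plus max. 3 months) of intervention (V2". Intervention description {11a} adds that "the duration of the intervention can be extended up to a maximum of 9 months". Eligibility criteria {10} admit "Infants and children aged 8 months to 4 years with a sensitization".
- **Model.** Statistical methods {20a} analyse secondary endpoints with treatment group and the stratification factors, using logistic regression for binary endpoints. The baseline value is mentioned only in this clause: "continuous endpoints will be analyzed by analysis of covariance (ANCOVA) with the respective baseline value (if available) as an additional covariate".
- **Existing wheeze.** Relevant concomitant care {11d} lets participants continue their usual medications and "those taken for any concomitant diseases including wheezing and eczema throughout the study". Children with wheezing can therefore take part.
- **Data collected.** Table 3 schedules medical history and physical examination at both V1 and V2. It has no row for asthma or for wheezing.

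**The concern.** Two things look wrong, and the first carries the point.

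First, the article prints an objective and a full endpoint list that disagree. Readers who see a wheezing result reported under the published objective would take it as a result on asthma prevalence. Nothing in the document links wheezing, over a few months in infants and preschool children, to an asthma definition.

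Second, wheeze before enrolment is likely to predict wheeze at V2. The plan uses the baseline value where the endpoint is continuous and not where it is binary, with no reason given. If wheezing is binary, its model leaves out what is probably its strongest predictor.

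The primary endpoint, the confirmatory test and the sample size are not affected.

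**Working it through.** **Step 1: objectives against endpoints.** Both lists are in the article, so they can be matched item by item.

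| Objectives {7} | Matching item in Secondary endpoints |
|---|---|
| Allergic reactions | Immediate-type allergic symptoms |
| Gastrointestinal problems | Gastrointestinal symptoms |
| Multiple food allergies | Multiple food allergies; number of food allergies |
| Eczema severity | SCORAD and EASI, each as change from baseline |
| Immunoglobulin pattern | Allergen-specific IgE |
| Asthma prevalence | None; nearest item is wheezing |

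Asthma is the only unmatched objective. Table 2 defines food allergy only, and Table 3 has no asthma assessment. In the subgroup section {20b}, asthma appears only as a parental disease.

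**Step 2: baseline wheeze in the model.** The stratification factors under Sequence generation {16a} are primary allergen, age group, grade of sensitization and planned duration. None measures wheeze. Under the rule in {20a}, a binary wheezing model therefore has no baseline wheeze term.

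**Step 3: the analysed sample.** The document gives no wheezing figure to reproduce, so I take its sample size as the base. For 35% vs. 60%, two-sided 5% and 80% power, with mean rate 0.475:

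n = [1.960·√(2·0.475·0.525) + 0.842·√(0.35·0.65 + 0.60·0.40)]² / 0.25² ≈ 61.4, rounded up to 62 per group.

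Power at 62 per group is 80.4%, and 124/0.90 = 137.8 gives 138. The plan's figures reproduce.

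**Step 4: what the missing covariate costs.** All wheeze inputs are assumptions:
- baseline wheeze in 20–35% of children;
- V2 wheeze on placebo in 50–60% of those children and 10–15% of the rest;
- the same treatment odds ratio in both groups of children;
- 62 per arm and a likelihood-ratio test at two-sided 5%.

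At an odds ratio of 0.35, with 4,000 simulated trials per row:

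| Baseline wheeze | V2 wheeze, with / without baseline wheeze | Power without covariate | Power with covariate | Gain (points) |
|---|---|---|---|---|
| 20% | 60% / 10% | 38.1% | 44.0% | 5.9 |
| 20% | 50% / 15% | 48.1% | 50.1% | 2.0 |
| 35% | 60% / 10% | 43.7% | 53.4% | 9.7 |
| 35% | 50% / 15% | 53.8% | 57.8% | 4.0 |

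An odds ratio of 0.35 is optimistic for wheezing. It is close to the effect planned for food allergy: (0.35/0.65)/(0.60/0.40) = 0.36. With weaker effects over the same ranges (3,000 trials per scenario):
- **Odds ratio 0.5:** power 21–29% without and 25–33% with the covariate, a gain of about 1 to 6 points.
- **Odds ratio 0.7:** power 9–12% without and 11–13% with it, a gain of about 1 to 2 points.

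**The case against.** **The article is abridged.** It says so, and it leaves further analysis details to an SAP that is not shown. The definition of wheezing and the exact covariates may be there, and {20a} does not forbid a baseline term in a logistic model. This stands for the definition and weakens the covariate part. It does not remove the first part, because the objective and the endpoint list are both published here and disagree.

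**Existing wheeze counted as outcome.** A reader might infer that children already wheezing at entry are simply counted as events. The document does not say so. It does not define wheezing, state whether it is new or any wheeze, or call it binary. The objective also speaks of prevalence, which properly includes existing cases. For scale only, suppose new wheeze is 10% vs. 20% and a share b of both arms wheezes at baseline and still does at V2. The rates become b + (1 − b)·0.10 and b + (1 − b)·0.20. At b = 20% these are 28% and 36%, and the odds ratio moves from 0.44 to 0.69. Unadjusted power falls from 34% to 16%; among children without baseline wheeze it is 28%. That describes dilution of an effect on new wheeze, a question the objective does not ask.

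**Bias.** A reader might also infer that leaving out baseline wheeze biases the comparison. It does not. Allocation is randomized 1:1, so baseline wheeze is balanced in expectation and the test stays valid. The unadjusted odds ratio is a marginal one, typically nearer to 1 than the adjusted one, but that is a difference in target.

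**Availability.** V1 wheeze status is not named as a recorded item. Medical history and examination are done at both visits and are its most plausible source, but this is an assumption.

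**Consequence.** Everything except the primary analysis is exploratory, no sample size was set for wheezing, and at an odds ratio of 0.5 or weaker the covariate does not rescue an underpowered comparison. This stands and limits the severity.

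**Conclusion.** The mismatch holds on the face of the document. An asthma objective is stated, no asthma endpoint exists, and wheezing assessed at V2 after 3–9 months in children enrolled at 8 months to 4 years cannot stand in for it. The trial as described cannot conclude anything about asthma prevalence.

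The covariate part is secondary and conditional. If wheezing is analysed as binary under the stated rule, some precision is lost, about 1 to 10 percentage points of power over the assumed rates and odds ratios of 0.35 to 0.7. The upper end needs an effect as large as that planned for food allergy. Severity is minor.

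**What to change.** 1. In Objectives {7}, replace asthma prevalence with wheezing, stating whether it is wheezing at V2 or during the intervention, and make no asthma claim in the report.
2. In {20a}, extend the rule on using the baseline value where available to binary endpoints, so that V1 wheeze status enters the wheezing model.
3. As a supplementary summary, describe new wheeze by arm among children without wheeze at V1.

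The cost is the wording of one objective, one extra term in an exploratory model, and extracting V1 wheeze status from the medical history. No visit or sample is added.

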### Trial design {8}

This is a randomized, placebo-controlled, double-blind, superiority, single-center trial with two parallel groups (Fig. 1). Allocation of subjects will be performed in a concealed fashion by authorized site personnel using a REDCap database. Each participant will be allocated to 1 out of 20 kit codes for the corresponding allergen(s) for the interventional product (10 codes active, 10 codes placebo).

**Fig. 1 Fig1:**
[figure not shown]
Study design overview. The diagram shows the flow of the patients after enrollment and randomization in the active group or the placebo group. Subjects in the active group will receive a sugar-free rusk-like biscuit powder(s) containing the target food(s) (hen’s egg, cow’s milk, peanuts, and/or hazelnuts) against which they are sensitized with unknown clinical relevance while subjects in the placebo group will receive a sugar-free rusk-like biscuit powder(s) without any of these allergens. After 3 to 6 months of intervention, all subjects will undergo an oral food challenge against the target food(s)

TIFFANI is part of the clinical research unit (CRU) 339 “food allergy and tolerance” (FOOD@).

## Methods: participants, interventions, and outcomes

### Study setting {9}

This single-center trial is recruiting participants at the inpatient and outpatient unit of the Department of Pediatric Respiratory Medicine, Immunology and Critical Care Medicine Charité – Universitätsmedizin Berlin. All visits throughout the study will take place either in the study center (visit 1) or on the ward (visit 2: oral food challenge).

### Eligibility criteria {10}

Infants and children aged 8 months to 4 years with a sensitization (specific IgE (sIgE) ≥ 0.1 kU/l and/or skin prick test (SPT) wheal size ≥ 3 mm) against cow’s milk, hen’s egg, peanuts, and/or hazelnuts (target allergenic foods) and an already scheduled oral food challenge at the Charité – Universitätsmedizin Berlin (3–6 months after enrollment) for routine diagnostics are eligible for the trial. Infants are excluded from the study if they have previously consumed the target allergenic food they are sensitized to in relevant amounts. Further exclusion criteria are wheat allergy (study product contains wheat), severe other health issues (e.g., heart disease), a twin sibling already taking part in the study, and participation in another interventional trial.

### Who will take informed consent? {26a}

The legal representative(s) of all participants must read, sign, and date the informed consent form before entering the study or undergoing any study-specific procedures. Before consent is given, the investigator or his/her representative will explain verbally the aim, method, source of funding, and the anticipated benefits and potential risks of the study to the parents; answer all questions regarding the study; and document the informed consent process.

